## Abstract

**Background:**

Parental donor kidney transplantation is the most common treatment option for children and adolescents with kidney failure. Emerging data from observational studies have reported improved short- and medium-term allograft outcomes in recipients of paternal compared to maternal donors. The INCEPTION study aims to identify potential differences in immunological compatibility between maternal and paternal donor kidneys and ascertain how this affects kidney allograft outcomes in children and adolescents with kidney failure.

**Methods:**

This longitudinal observational study will recruit kidney transplant recipients aged ≤18 years who have received a parental donor kidney transplant across 4 countries (Australia, New Zealand, United Kingdom and the Netherlands) between 1990 and 2020. High resolution human leukocyte antigen (HLA) typing of both recipients and corresponding parental donors will be undertaken, to provide an in-depth assessment of immunological compatibility. The primary outcome is a composite of de novo donor-specific anti-HLA antibody (DSA), biopsy-proven acute rejection or allograft loss up to 60-months post-transplantation. Secondary outcomes are de novo DSA, biopsy-proven acute rejection, acute or chronic antibody mediated rejection or Chronic Allograft Damage Index (CADI) score of > 1 on allograft biopsy post-transplant, allograft function, proteinuria and allograft loss. Using principal component analysis and Cox proportional hazards regression modelling, we will determine the associations between defined sets of immunological and clinical parameters that may identify risk stratification for the primary and secondary outcome measures among young people accepting a parental donor kidney for transplantation. This study design will allow us to specifically investigate the relative importance of accepting a maternal compared to paternal donor, for families deciding on the best option for donation.

**Discussion:**

The INCEPTION study findings will explore potentially differential immunological risks of maternal and paternal donor kidneys for transplantation among children and adolescents. Our study will provide the evidence base underpinning the selection of parental donor in order to achieve the best projected long-term kidney transplant and overall health outcomes for children and adolescents, a recognized vulnerable population.

**Trial registration:**

The INCEPTION study has been registered with the Australian New Zealand Clinical Trials Registry, with the trial registration number of ACTRN12620000911998 (14th September 2020).

## Background

Kidney transplantation is the treatment of choice for people with kidney failure, conferring a significant survival advantage compared to people treated with long-term dialysis [1]. Live donor kidney transplantation is preferred because survival rates of patients and allografts are substantially longer in comparison with deceased donor transplants [2–4]. In addition, living donation facilitates pre-emptive transplantation, avoiding the deleterious effects on health, psychosocial and educational outcomes of dialysis treatment on children during critical periods of growth and development [3].

Most pediatric and adolescent kidney transplant recipients require subsequent transplants and following allograft failure are often highly sensitized (with development of multiple anti-human leukocyte antigen [HLA] antibodies that may hinder future transplant potential) and at higher risk of death [5]. Selecting the donor kidney associated with the best possible long-term allograft outcome is vital. Parental donors account for over 60% of live donor kidneys for pediatric and adolescent patients with kidney failure in the United Kingdom, Australia and New Zealand [6, 7]. However, it is unclear whether maternal versus paternal donation is associated with differential allograft outcome. A recent population cohort study showed that kidney transplants from maternal donor kidneys were associated with an up to a 60% greater risk of acute rejection and allograft loss compared to paternal donor kidneys [8]. This finding is contradictory to the previously held paradigm that exposure to non-inherited maternal antigen (NIMA) may incite a lesser immunological response compared to exposure to non-inherited paternal antigen (NIPA). Previous cohort studies and experimental models have suggested that exposure of a child to the NIMA during pregnancy may lead to NIMA-specific tolerance. In one study, sibling transplants expressing NIMA were associated with lower risk of rejection and superior allograft outcomes compared to transplants expressing the NIPA [9–11]. Given that parental donors are the predominant source of live donor kidneys for pediatric and adolescent patients with kidney failure, this study will help inform whether HLA matching at the epitope, amino acid and physiochemical properties level may enhance the understanding of the differential antigenicity and immunogenicity of NIMA and NIPA on allograft outcomes following parental donor kidney transplantation. The findings from this study may potentially have important clinical implications in the selection of the appropriate parental donor kidney for transplantation.

The over-arching objective of this study is to address the current knowledge gap of the “NIMA paradox” by identifying potential differences in immunological compatibility between maternal and paternal donor kidneys and how this compatibility affects allograft outcomes. The study aims include:(i)Detailed immunological profiling for pediatric and adolescent recipients of parental donor kidneys with and without adverse allograft outcomes of the development of de novo donor-specific anti-HLA antibody (DSA), any acute rejection or allograft loss;(ii)Determine the association between different immunological risk profiles and adverse allograft outcomes; and(iii)Determine whether the associations between the immunological risk profiles and adverse allograft outcomes are modified by parental status and other clinical factors.

## Methods/design

### Study design and setting

The INCEPTION study is a longitudinal observational study that will recruit pediatric and adolescent transplant recipients aged ≤18 years who have received parental donor kidneys between January 1990 and December 2020 (Fig. 1). Corresponding parental donors will also be recruited for inclusion in the study. Adult kidney transplant recipients of parental donor kidneys aged > 18 years at time of transplantation or recipients of deceased donor kidney transplants will be excluded. Funding for the INCEPTION study is provided by the National Health and Medical Research Council (NHMRC) Ideas Grant (Application ID: APP1184595, funding duration 2020-2023), the Department of Health Western Australia and the Telethon-Perth Children’s Hospital Research Fund (funding duration 2017-2020) and Starship Foundation Clinical Research Grant (Auckland, New Zealand). The reporting and conduct of the study will adhere to The Strengthening the Reporting of Observational studies in Epidemiology (STROBE) guidelines [12].

**Fig. 1 Fig1:**
[figure not shown]
Design, participants and outcome measures of the INCEPTION study

This study will be conducted across 4 countries including Australia (5 transplant centres), New Zealand (1 transplant centre), United Kingdom (UK, 13 transplant centres) and the Netherlands (3 transplant centres). The INCEPTION study has been registered with the Australian New Zealand Clinical Trials Registry (ANZCTR) prior to recruitment, with the trial registration number of ACTRN12620000911998 (registration approved 14th September 2020).

### Study recruitment and data capture

In Australia and New Zealand, parental donor-recipient pairs that fulfil the inclusion criteria will be identified through the Australia and New Zealand Dialysis and Transplant (ANZDATA) registry and forwarded to local site investigators. Only donor-recipient pairs recorded in the registry as living and residing in Australia and New Zealand will be approached for participation. Each donor-recipient pair will provide written or verbal informed consent or age-appropriate assent by the site study investigators or delegates before participation. The Sir Charles Gairdner Osborne Park Health Care Group Human Research Ethics Committee (Perth, Western Australia, Australia) approved the research application in December 2018, with reciprocal ethics approvals covering all participating sites in Australia and New Zealand. Consent for New Zealand participation was obtained from the New Zealand Health and Disability Ethics Committee (Ministry of Health, Wellington, New Zealand). Verbal consent will be utilized during the current pandemic of COVID-19 infection, with the HREC of each participating site granting the approval to this amendment if appropriate. In the United Kingdom (approval from the United Kingdom National Health Service [NHS] in England and Wales) and the Netherlands (approval from the Medical Ethics Review Committee of the Amsterdam Academic Medical Center), project-specific waiver of consents for serum or deoxyribonucleic acid (DNA) biobanking and conduct of research studies relating to kidney transplant outcomes have been granted, and the conduct of this study have received updated ethics approvals.

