### Study procedure

In Australia and New Zealand, all consented donor-recipient pairs will attend a single study visit to have 20 mL of blood drawn for separation into serum/plasma and deoxyribonucleic acid (DNA) isolation. This blood sampling will be taken from all donor-recipient pairs regardless of the availability of prior stored serum/plasma and DNA for testing. The timing of this additional blood test for recipients will coincide with their routine clinical blood withdrawal where possible. Donor and recipients will also consent to allow access of their health records from ANZDATA registry (or equivalent healthcare registries in other countries), Organ Matching (Australia-specific) and other country-specific Blood Service systems (a computer data system that stores information relating to organ allocation and donor kidney details, including information on donor and recipient HLA typing and pre-transplant and de novo DSA) and local health records from their respective hospitals. For donor-recipient pairs in the UK and the Netherlands, the ethics approval will allow for the utilization of the stored serum/plasma and DNA for testing (where required), with no additional blood sampling to be requested from these pairs.

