### Outcome measures

The primary outcome is the composite of de novo DSA (defined as mean fluorescence intensity [MFI] of over 500), or any biopsy-proven acute rejection or allograft loss (defined as returning to dialysis or death with functioning allograft) after parental donor kidney transplantation up to 60-months post-transplant. Secondary outcomes are individual components of the primary composite outcome (development of de novo DSA, any biopsy-proven acute rejection, allograft loss at 60-months post-transplant but also extended follow-up to 120-months post-transplant), acute or chronic AMR (including the presence of TG) or Chronic Allograft Damage Index (CADI) score of > 1 on allograft biopsy post-transplant, allograft function (creatinine-derived estimated glomerular filtration rate [eGFR] using the Chronic Kidney Disease-Epidemiology Collaboration [CKD-EPI] equation for recipients aged ≥16 years [32] or bedside Schwartz equation for recipients aged < 16 years [33–35]), and urine proteinuria.

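### Australia and New Zealand approach only living pairs, so death with a functioning graft, part of the 60-month primary outcome, cannot be observed there for transplants whose window closed before contact

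*Protocol article*

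**What the plan says.** All references are to the protocol article.

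- **Who is approached.** Under Study recruitment and data capture: "Only donor-recipient pairs recorded in the registry as living and residing in Australia and New Zealand will be approached for participation". Study procedure adds consent and a visit: "This blood sampling will be taken from all donor-recipient pairs regardless of the availability of prior stored serum/plasma and DNA for testing".
- **Which transplants.** Under Study design and setting, recipients are those "who have received parental donor kidneys between January 1990 and December 2020".
- **The outcome.** Outcome measures defines the third component of the primary composite as "allograft loss (defined as returning to dialysis or death with functioning allograft", counted "after parental donor kidney transplantation up to 60-months post-transplant".
- **Mortality after graft failure.** Background says that recipients whose graft has failed are often highly sensitized and "at higher risk of death".
- **The other two countries.** UK and Dutch pairs enter under a "project-specific waiver of consents for serum or deoxyribonucleic acid (DNA) biobanking", using stored material and no new blood sample. No condition that the pair be alive is stated. Inclusion of deceased pairs is not stated either.
- **Use of the cohorts.** Statistical analysis derives the archetypes in Australia and New Zealand, using time from transplant to the composite. It validates them in the UK and Dutch cohorts, pools all cohorts in the Cox model, and compares predicted with observed deaths.

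**The concern.** Follow-up starts at transplant, but membership of the Australian and New Zealand cohort is decided years later by being alive. A recipient who died with a functioning graft had a primary-outcome event, and that same event keeps the recipient out of the study. Delayed-entry methods do not help where contact comes after month 60, because no at-risk time remains inside the outcome window.

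The risk profiles are derived in this cohort and then tested in cohorts for which no such rule is stated. A shortfall of events in derivation could therefore look like poor calibration in validation, and deaths predicted from a survivors-only cohort would be too few. The same pairs also enter the combined Cox model.

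**Working it through.** **1. Transplant years affected (from the text alone).** The study was registered in September 2020, before recruitment, so contact is no earlier than that. September 2020 minus 60 months is September 2015. January 1990 to September 2015 is about 25.7 of the 31 calendar years. In those years no in-window death can be recorded in Australia or New Zealand. This counts years, not recipients. For later transplants, deaths before contact are lost too, but part of the window may remain open.

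**2. The plan's own figures.** Sample size calculation assumes a composite of up to 40% and a difference of 0.10. With 0.40 against 0.30, 80% power, two-sided 5% and continuity correction, a single observation needs 376 per arm (752 in total). Four observations with correlation 0.5, each missing with probability 0.10, carry expected information Σ P(k)·k/[1+(k−1)·0.5] = 1.556 per subject. Then 752/1.556 = 483, within 1% of the stated 479. The sample size is not at issue here. The 40% is the base for what follows.

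**3. Shift in graft loss and in the composite (mortality inputs assumed).** Assume true 60-month graft loss of 12%, a further 28% with DSA or rejection only, and 60% with no event. Let a1 be the proportion alive at contact among those with graft loss (averaged over deaths, none of whom survive, and returns to dialysis). Let a0 be the proportion alive among everyone else.

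- Observed loss = 0.12·a1 / (0.12·a1 + 0.88·a0)
- Observed composite = (0.12·a1 + 0.28·a0) / (0.12·a1 + 0.88·a0)

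| a1 / a0 | Observed loss (true 12%) | Observed composite (true 40%) |
|---|---|---|
| 0.90 / 0.97 | 0.1080/0.9616 = 11.2% | 0.3796/0.9616 = 39.5% |
| 0.80 / 0.95 | 0.0960/0.9320 = 10.3% | 0.3620/0.9320 = 38.8% |
| 0.70 / 0.92 | 0.0840/0.8936 = 9.4% | 0.3416/0.8936 = 38.2% |

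Graft loss is understated by 6% to 22% in relative terms. The composite moves by 0.5 to 1.8 points.

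**4. Harsher assumptions.** Let every type of composite event carry extra mortality, with m1 = 0.05 to 0.30 dead before contact among those with an event and m0 = 0.01 to 0.05 among the rest. The observed composite is 0.40(1−m1) / [0.40(1−m1) + 0.60(1−m0)]. It stays at 0.40 when m1 = m0 and falls to 0.280/0.874 = 0.32 at m1 = 0.30, m0 = 0.01.

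**5. Graft loss split into its two parts.** Assume true loss of 0.10, of which 0.01 to 0.03 is death with function.

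- Only those deaths removed: 0.09/0.99 = 0.091 to 0.07/0.97 = 0.072 (9% to 28% understatement).
- 30% of those back on dialysis also dead before contact: 0.063/0.963 = 0.065 to 0.049/0.949 = 0.052.

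**6. The maternal-paternal contrast.** Take 0.45 against 0.35 with m1 = 0.30 and m0 = 0.01 for both parents. The observed proportions are 0.315/0.8595 = 0.3665 and 0.245/0.8885 = 0.2757, a difference of 0.091 instead of 0.10. The odds ratio is 1.52 before and after, because the factor (1−m1)/(1−m0) multiplies both odds and cancels. Distortion of the odds ratio needs survival to contact to depend jointly on outcome and on parent or profile.

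**The case against.** The restriction is openly stated, follows from consent, and sits in an observational study to be reported under STROBE. Weighting and sensitivity analyses may be in a fuller plan that is not shown. The aims are associations, and selection on outcome alone lowers incidence without changing an odds ratio. Those points stand, and they limit the size of the problem. They do not remove it: the enrolment rule and the outcome definition are both fixed in this article, and together they make one component unobservable in most transplant years of one cohort.

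Four stronger readings are tempting, and the documents do not support them.

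- **A reader might infer that graft failures in general are removed, and from the derivation cohort only.** Only recipient deaths before contact are removed with certainty. Returns to dialysis, rejection and DSA are lost only where the recipient later died. The article does not say that deceased UK or Dutch pairs are included, and dependence on stored samples may select in its own way.
- **A reader might infer that the two sets of countries have different outcome definitions.** There is one definition. What may differ is selection.
- **A reader might infer that the maternal-paternal contrast is biased.** Requiring a living donor could select mothers and fathers differently, but nothing in the article shows that it does.
- **A reader might infer that donor deaths deepen the graft-loss shortfall.** They would do so only if donor death were associated with graft loss, for which the article gives no evidence.

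**Conclusion.** The point holds as a conflict between an enrolment rule and a primary-outcome component. From the text alone, death with a functioning graft within 60 months cannot be observed in Australia or New Zealand for transplants more than 60 months before contact. Absolute risk, calibration and the comparison of predicted with observed deaths are exposed.

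The shift in the 40% composite is probably modest: about 0.5 to 2 points under the moderate survival rates assumed above, and up to 8 points under the harshest. The graft-loss component suffers more in relative terms. Every size rests on assumed mortality, since the article gives none. An effect on the maternal-paternal contrast remains possible and unproven.

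**What to change.** 1. For the derivation and validation step and for the combined Cox model, use a composite with death-censored graft loss (return to dialysis only). Keep the composite that includes death as a sensitivity analysis.
2. Repeat the UK and Dutch analysis restricted to recipients alive at a calendar date comparable with contact in Australia and New Zealand. Apply the same restriction to donors where their vital status is known; it is not among the donor variables listed under Clinical and laboratory parameters.
3. Do not report death with functioning graft, or mortality calibration, from Australian and New Zealand transplants whose window closed before contact.
4. Where approvals allow, compare participants with all eligible ANZDATA pairs by era, age, parent, rejection and graft failure, and use inverse-probability-of-inclusion weights as a sensitivity analysis. Record access is described as consent-based, so this may need approval. ANZDATA holds no de novo DSA data, so the weights cannot use that component.

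**Cost.** Items 1 to 3 change the analysis only. At 520 pairs and a 40% composite there are about 208 events. If 1% to 3% of recipients die with function, death-censoring drops at most 520 × 0.01 ≈ 5 to 520 × 0.03 ≈ 16 of them, fewer where DSA or rejection came first, and intervals widen slightly. None of these steps recovers the excluded deaths, and death-censoring aligns the endpoint without removing selection on survival, so the remaining survivor selection must be stated as a limitation. A consent waiver for deceased pairs is optional: early pairs may lack high-resolution typing or usable DNA, and the fix does not depend on it.

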### Study procedure

In Australia and New Zealand, all consented donor-recipient pairs will attend a single study visit to have 20 mL of blood drawn for separation into serum/plasma and deoxyribonucleic acid (DNA) isolation. This blood sampling will be taken from all donor-recipient pairs regardless of the availability of prior stored serum/plasma and DNA for testing. The timing of this additional blood test for recipients will coincide with their routine clinical blood withdrawal where possible. Donor and recipients will also consent to allow access of their health records from ANZDATA registry (or equivalent healthcare registries in other countries), Organ Matching (Australia-specific) and other country-specific Blood Service systems (a computer data system that stores information relating to organ allocation and donor kidney details, including information on donor and recipient HLA typing and pre-transplant and de novo DSA) and local health records from their respective hospitals. For donor-recipient pairs in the UK and the Netherlands, the ethics approval will allow for the utilization of the stored serum/plasma and DNA for testing (where required), with no additional blood sampling to be requested from these pairs.

### Defining detailed donor-recipient immunological risk profiles

#### High resolution HLA typing

Over the last decade, HLA-typing has evolved from serological typing to high resolution molecular typing covering HLA-A, −B, −C, −DRB1/3/4/5, −DPA1, −DPB1, −DQA1 and -DQB1 loci, providing a more comprehensive and accurate assessment of tissue compatibility in transplantation. High-resolution molecular HLA typing for the 11 HLA-loci will be performed using a Next Generation Sequencing (NGS) or an alternative high-resolution typing technique by the respective tissue typing laboratories in each country. Given NGS HLA-typing across all HLA alleles is considered standard practice for living donor transplantation in many transplanting centers, re-typing of donors/recipients will not be undertaken unless typing across all HLA alleles at the high-resolution level is not available.

#### Quantifying HLA-eplet mismatches

Epidemiological studies have consistently shown an association between an increasing number of epitope or eplet mismatches and an increased risk of adverse allograft outcomes, including the development of de novo DSA, antibody mediated rejection (AMR), transplant glomerulopathy (TG) and/or premature allograft loss [13, 14]. High-resolution molecular typing provides the opportunity for a more comprehensive and accurate assessment of HLA compatibility in transplantation. However, compatibility based on the many thousands of HLA alleles is fundamentally impossible, but the variation in HLA alleles can be explained by differences in a relatively low number of epitopes, which are part of the HLA protein, made up of polymorphic amino acid residues. Eplets are short discontinuous sequences of amino acid residues within each HLA epitope that can theoretically elicit a B-cell driven immune response in the recipients (immunogenicity) [15, 16]., Therefore, compatibility assessment focusing on eplet mismatches, calculated using a computer program known as HLAMatchmaker [16, 17], is likely to have the potential to improve prediction of adverse allograft outcomes [18]. The identification and quantification of the respective location and number of eplet mismatches at HLA class I (HLA-A, −B, −C) and class II (HLA-DRB1/3/4/5, −DPA1, −DPB1, −DQA1 and -DQB1) loci will be determined by entering the 2-field molecular HLA typing for each donor and recipient pair into the HLAMatchmaker to enable a comparison of the HLA eplet-profiles of each donor/recipient pair (HLA-ABC v2.0 and HLA-DRDQDP v2.1; http://www.eplets.net).

